## Discussion

Adolescence is a critical phase of human development where mental health problems, particularly ADs, are highly prevalent (e.g., [3, 4]) and often persist and/or develop into other disorders throughout an individual's life (e.g., [14, 21]). Even if growing evidence points to the importance of understanding the common mechanisms underlying mental health conditions (e.g., [31]), research focusing on adolescents is worryingly limited. Indeed, while PI/PF processes have been largely investigated and ACT has demonstrated to be effective for multiple conditions in adults (e.g., [35, 42]), adolescent populations have been consistently overlooked (e.g., [27–30]). Thus, this project aims to explore the conceptual foundations and therapeutic application of ACT in this pivotal phase of human development. We will delve into the relationships between PI/PF processes, anxiety and flourishing in various adolescents’ samples, and investigate the efficacy of ACT for GAD and SAD in this developmental life stage.

To the best of our knowledge, this is the first project that proposes to comprehensively examine all PI/PF processes in testing ACT assumptions as accurate theoretical conceptualizations of anxiety and flourishing in community adolescents, resorting to network analysis (Study I). Drawing on the theoretical propositions and studies using network approaches to explore associations between PI/PF and mental health outcomes (e.g., [47, 49]), we expect PI processes to display interrelationships and associate positively with anxiety and negatively with flourishing in adolescents from the community. Similarly, PF processes are expected to interconnect with each other and associate negatively with anxiety and positively with flourishing in that community sample. By exploring the strongest and most influential ACT processes in the networks, we will be able to better understand the unique contribution of each PI/PF process within a system, either to flourishing or to anxiety. For example, understanding which process may influence a greater number of other processes, or more strongly impact specific mental health outcomes (e.g., anxiety, flourishing), may help clinicians to increase interventions’ impact. Furthermore, differences in the paths linking PI/PF processes to anxiety and flourishing in clinical (SAD and GAD) and mentally healthy samples of adolescents (Study II) will be explored by testing model invariance. We expect similar pathways linking PI/PF processes to anxiety and flourishing across all groups (i.e., SAD clinical, GAD clinical and mentally healthy groups), with distinct mean levels observed between the clinical and the mentally healthy groups. This would be in line with existing research with adolescents supporting the associations between PI/PF and positive (e.g., [55, 57]) and negative (e.g., [52, 54]) mental health outcomes in clinical (e.g., [53]) and non-clinical samples (e.g., [51]), though not specifically applied to GAD and SAD in adolescence. Moreover, if confirmed, these results will further sustain the role of PI/PF towards adolescents’ mental health, also under a transdiagnostic framework. By investigating specific associations between all PI/PF processes and anxiety as well as flourishing across clinical samples, this research project will provide valuable insights into the necessity for process sensitivity assessment, which may contribute to the development of more tailored and, hopefully, more impactful and idiosyncratic interventions for adolescents.

Additionally, this project will investigate the efficacy of ACT delivered online via videoconferencing to adolescents with SAD and GAD, compared to a control group. The online delivery of ACT is a relevant strength of this research project. The efficacy of full synchronous online ACT interventions delivered to adolescent SAD and GAD have not yet been investigated. However, this method of delivering interventions may be particularly relevant to adolescents as it is more accessible and it may help to circumvent obstacles to treatment seeking such as autonomy (i.e., being dependent on parents/adults to drive them to clinics), time and money spent on commuting and fear of stigmatization when seeking in-person psychological support [94]. Moreover, adolescents spend more time online than any other age group, and so online interventions have the potential of being a well-received method, thus enhancing the delivery of mental health care within this adolescence [95].

By using a robust RCT design to investigate the efficacy of ACT, this project will address the scarcity of methodologically robust designs examining that topic specifically in relation to mental health conditions in adolescents (e.g., [27–30, 65]). We will also compare the efficacy of the same ACT intervention between GAD and SAD clinical groups, expecting similar effects on outcome measures. Moreover, we will investigate the maintenance of intervention gains over time, which will offer a better understanding of the utility of ACT during a period of significant and rapid physical, psychological, and social changes. If the intervention is found to be efficacious, this project will support the future delivery of ACT interventions to adolescent ADs as a reliable transdiagnostic alternative, and as an added option for those who do not achieve desired results from standard treatments. This may offer clinicians the opportunity to choose interventions based on adolescents needs, while adhering to evidence-based treatments and benefiting from the practical and economical implications of transdiagnostic approaches in clinical practice.

Finally, to the best of the authors' knowledge, this project will be the first to explore mechanisms of change following an ACT intervention for adolescents with SAD and GAD. We will consider all PI/PF processes, providing a more comprehensive examination of potential change mechanisms. This finding will further support the theoretical consistency of the ACT model and shed light on the processes responsible for change, thereby expanding the reach and benefits of ACT interventions. Based on previous research on the relevance of the ACT processes [43, 44] and on the transdiagnostic model underlying ACT (e.g., [37, 38]), we expect changes to those processes to predict changes in flourishing and anxiety symptoms similarly in both clinical intervention groups. From an ACT perspective ([39, 38]), adaptative behavioral change results from reducing inflexible patterns in which private events heavily influence action taking, distancing individuals from a valued living (PI) through cultivating the ability to fully contact the present moment as it is and persist in and/or change behavior in ways that bring meaning and vitality to one’s life (PF). Therefore, we expect decreases in PI processes and increases in PF processes to account for higher levels of flourishing and lower levels of anxiety following the intervention. This expectation aligns with the clinical features of many anxiety disorders, such as GAD and SAD, where avoidance of anxiety-triggering situations and rumination about future events are key maintenance factors encompassed within PI processes such as inaction, impulsivity, or avoidant persistence, and dominance of the conceptualized past/feared future. About specific PI/PF process, equal importance is attributed to them within the ACT framework, as the inflexible/flexible patterns of responding to internal experiences and contextual cues and engaging in unworkable/workable behaviors result from the interdependent interactions among them that sustain overall PI/PF ([38]). For instance, helping adolescents see their thoughts as mental events rather than literal representations of reality (cognitive defusion), may help foster present moment awareness which, in turn, creates space for them to choose to avoid less anxiety triggering situations and take more contextual useful and values guided actions [96]. At the empirical level, it remains unclear the extent to which each individual PF/PI process may be more or less important to promote change, particularly while accounting for all model processes (see [43] for a review). Thus, we did not make specific predictions about which PI/PF processes would most influence change in anxiety or flourishing, as all processes are expected to contribute to change.

This study presents some foreseen limitations that are, nevertheless, necessary for its viability. Firstly, it focuses solely on SAD and GAD, disregarding other ADs that also present significant prevalence rates and impairments during adolescence. Additionally, the control group will not receive intervention within this project. To ensure these adolescents receive appropriate care, they will be assessed after completing the control condition and referred to school psychology services if difficulties persist. They will also be explicitly informed about the possibility of discontinuing their participation in the study to seek treatment, without any consequences. It is also important to note that the control group may not be entirely comparable to either of the intervention groups, which could lead to inherent disparities and the introduction of potential confounding variables. Based on ACT transdiagnostic premises, we believe that these differences will not significantly influence our findings. Nevertheless, the authors have devised a contingency plan to address this potential limitation, if necessary (i.e., gathering two independent control groups: one consisting solely of adolescents with SAD and another comprising only adolescents with GAD). We also acknowledge that by only using self-report measures, data collection may be susceptible to the effects of social desirability, and only a limited comprehension of the psychological constructs assessed is provided. Moreover, we anticipate dropouts to be a significant challenge in this study. To prevent its impact, the research team plans to recruit more participants than the minimum needed for each condition. This approach will allow us to account for potential attrition and ensure that sample size remains adequate throughout the study, maintaining statistical power. Efforts will be made to engage and motivate participants throughout the duration of the study to maximize retention rates (e.g., by sending thank you messages after each assessment moment). Lastly, we acknowledge that by not considering a group with comorbid GAD and SAD, we cannot fully elucidate the applicability of transdiagnostic principles to adolescents. Future research should consider comorbidity and/or cascading effects of mental health difficulties as relevant outcomes to better address the complex issues related to ACT as applied to adolescent mental health.

Albeit these anticipated limitations, we believe that this project holds great relevance in advancing knowledge of transdiagnostic processes underlying psychological functioning in adolescents. It also has the potential to inform and enhance the efficacy of interventions for this population. ACT shows promise as a therapy for adolescents with ADs (e.g., [60]), as its underlying transdiagnostic premises may help mitigate the impact of present and future mental health conditions. By exploring PI/PF processes in both clinical and non-clinical adolescent populations and testing the efficacy of ACT along with mechanisms of change, we will gain a better understanding of how (i.e., through which specific PI/PF processes) and for whom (i.e., GAD and SAD) ACT can contribute to adolescents’ mental health. This knowledge will ultimately contribute to the development of more effective and tailored interventions for this population, with the potential to improve their well-being and long-term mental health outcomes.

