### Study design and randomization of participants

The two aims of this research will be accomplished through diverse study designs. To accomplish the first aim, cross-sectional data will be collected from adolescents within a community sample, two clinical groups (with SAD or GAD), and a mentally healthy sample. For the second aim, a Randomized Controlled Trial (RCT) with a parallel design, 3 groups (i.e., Control Group, SAD Intervention Group, and GAD Intervention Group) and 4 assessment moments will be conducted following the CONSORT (Consolidated Standards of Reporting Trials) guidelines [77]. Adolescents from each clinical group from Study II will be randomly allocated (computer-generated random allocation,2:1 allocation ratio) to one of the intervention groups or to the control group. The two clinical intervention groups will receive the same intervention and will be assessed at pre- and post-intervention, and at 3- and 6- month follow-up using a set of self-report measures (see measures section). Adolescents from the control group will be assessed with the same set of self-report measures at 2 different time points (12 weeks interval), mimicking the pre- and post-intervention assessment moments. Given the high stability of both SAD and GAD, we consider ethical obligations to be imperative in not depriving these adolescents of intervention during follow-up assessments. As such, they will be assessed with a clinical structured interview (Mini-Kid; [78]) after the second time point and referred to the school psychology services if the difficulties persist. A flowchart of the study design is presented in Fig. 1.

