### Sample size

Participants recruited in Study II will be randomly assigned to one of the three groups of Study III (cf. Figure. 1). G*Power was used to calculate sample size considering Study III requirements for repeated measures analysis with two groups (considering that the RCT groups will be compared two at a time) and 4 assessment moments. Power analysis for medium effects (f = 0.25) – chosen based on previous ACT studies with adolescents (e.g., [27–30, 60, 80]) –, with a significance level of 0.05 and power of 0.95 requires a sample size of 25 per group. To account for the expected 17% dropout rate reported in a previous meta-analysis of ACT-based interventions [81], the research team intends to collect 4 additional participants per group. Accordingly, Study II will rely on two clinical groups (i.e., SAD and GAD,n ≥ 87) of at least 44 adolescents each, and a mentally healthy group of 29 adolescents (i.e., total n for Study II ≥ 116). For Study III, the clinical participants (i.e., n ≥ 87) will be then assigned to two intervention groups of 29 adolescents each, one for SAD and one for GAD participants, or to a control group of 29 adolescents, evenly distributed between adolescents presenting with SAD or GAD diagnoses.

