### Data analysis

IBM SPSS Statistics 25 will be used to conduct descriptive analysis. In study I, network analysis will be performed and visualized using R (Version 4.1.3). Network nodes will represent the scores for each PI/PF subscales and total scores for anxiety and flourishing measures. Edges will represent the weight of the correlations between the individual nodes. Centrality metrics (e.g., degree of centrality) will also be computed to investigate how important and influential each node is in the network. In study II, Mplus will be used to investigate the adjustment of a path analysis linking PI/PF processes to anxiety and flourishing, based on overall, comparative and residual based fit-indices. The moderator effect of groups (clinical SAD, clinical GAD and healthy adolescents) in those pathways will be estimated, testing for equality of pathways and means. In Study III, the IBM SPSS Statistics 25 will be used to explore treatment effects using Mixed ANOVAs and considering assessment moments as the within-subject and groups (SAD and GAD receiving intervention and Control Groups) as the between-subject effect; interaction effects will also be considered. Additionally, Mplus will be used to examine mechanisms of change after the intervention by performing two-wave latent change score models. These models allow to explore not only if significant changes emerged across assessment moments, but also to investigate the impact of changes in PI/PF constructs on changes in anxiety or flourishing. All Study III analyses will be carried out according to an intention-to-treat principle as suggested by the CONSORT guidelines [77]. Therefore, all participants randomized will be included in the statistical analyses and analyzed according to the group they were assigned regardless of having received/completed or not the intended intervention. Efforts will be made to obtain outcome data for all participants, even if they do not complete the intervention. If data is missing (e.g., participant refused to provide data, participant was unreachable, etc.) the last observation carried forward method will be employed.

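### Controls are told of care-seeking only as leaving the study, which sits badly with following everyone randomised and, under last observation carried forward, can bias both ACT-versus-control contrasts in a direction not known in advance

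*Protocol article*

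**What the plan says.** All references are to the protocol article.

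- **Discussion, limitations:** the control group receives no intervention within the project, and of these adolescents it says "They will also be explicitly informed about the possibility of discontinuing their participation in the study to seek treatment, without any consequences".
- **Study design and randomization of participants:** "Adolescents from the control group will be assessed with the same set of self-report measures at 2 different time points (12 weeks interval"), to mirror pre- and post-intervention. Planned referral comes later: controls are interviewed "after the second time point and referred to the school psychology services if the difficulties persist".
- **Data analysis:** under intention-to-treat, "all participants randomized will be included in the statistical analyses and analyzed according to the group they were assigned". On follow-up: "Efforts will be made to obtain outcome data for all participants, even if they do not complete the intervention". Where data are still missing, "the last observation carried forward method will be employed".
- **Sample size:** one control group of 29, split evenly between the two diagnoses, is planned alongside two intervention groups of 29. The 17% dropout allowance is taken from a meta-analysis of ACT-based interventions.
- **Measures:** the sociodemographic sheet already has a yes/no item on current or past psychological support.

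**The concern.** The Discussion mentions seeking treatment during the control period only as a reason to discontinue participation. Nowhere does the article say that a control may seek care and still answer the second questionnaires. Current treatment for a psychiatric condition is also an exclusion criterion at entry, so families and staff could easily conclude that treatment and participation do not go together.

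The follow-up sentence in Data analysis covers all participants, but its example is failure to complete the intervention, which controls do not have. Nothing links it to a control who has been told that leaving is the way to obtain care.

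Three features make this matter:

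- The reason for leaving is need for care, so the missingness is plausibly related to outcome, and this trigger is described for the control arm only.
- A control has only one earlier value to carry forward, the baseline.
- The same control group serves the SAD and the GAD comparison, so any distortion enters both.

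Recruiting extra participants protects power but does not correct this kind of bias. No later analysis plan can recover scores that were never collected.

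**Working it through.** **The plan's own figure.** The sample size is not in dispute but can be reproduced. The plan states f = 0.25, two groups, four moments, and "with a significance level of 0.05 and power of 0.95 requires a sample size of 25 per group". For a repeated-measures F test (within factor, or within-between interaction), λ = f²·N·m/(1 − ρ). The correlation ρ is not given. With ρ = 0.30 assumed and N = 50, λ = 0.0625 × 50 × 4 / 0.70 = 17.9 on 3 and 144 degrees of freedom, and power is 0.952. So 25 per group reproduces at ρ of about 0.30. For 17% dropout, 25/0.83 = 30.1 (31 per group) and 25 × 1.17 = 29.25; the plan uses 29. The allowance of four covers 4/29 = 13.8% loss.

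**Bias formula.** Let q be the share of controls who leave and are not reached, and c the 12-week improvement in SD that they would have shown if followed. Let q_A and a be the same for ACT dropouts. LOCF sets both groups to zero change, so relative to following everyone the contrast shifts by

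bias = q·c − q_A·a (positive favours ACT).

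The documents give none of these four quantities for this trial; all values below are assumptions. The q values are 4/29, the plan's 17%, and 30% as a high case.

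**No ACT dropout (q_A = 0):**

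| q | c = −0.25 | c = 0 | c = 0.25 | c = 0.5 |
|---|---|---|---|---|
| 0.138 | −0.034 | 0 | +0.034 | +0.069 |
| 0.17 | −0.043 | 0 | +0.043 | +0.085 |
| 0.30 | −0.075 | 0 | +0.075 | +0.150 |

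**ACT dropouts also carried forward** (q_A = 0.17, a = 0.5, so 0.085 is subtracted):

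- q = 0.17, c = 0.5: 0.085 − 0.085 = 0.
- q = 0.17, c = 0.25: 0.043 − 0.085 = about −0.04.
- q = 0.30, c = 0.5: 0.150 − 0.085 = +0.065.

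**Effect on the contrast.** Assume controls who stay improve 0.1 SD, ACT participants improve 0.6 SD, 17% of controls leave and no ACT participant does.

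- Leavers would improve 0.5 SD. Everyone followed: 0.6 − (0.83 × 0.1 + 0.17 × 0.5) = 0.43 SD. LOCF: 0.6 − 0.83 × 0.1 = 0.52 SD. In a simulation with 29 per arm the rejection rate was 36% with everyone followed and 53% with LOCF.
- Leavers would worsen by 0.25 SD. Everyone followed: 0.6 − (0.083 − 0.043) = 0.56 SD. LOCF is again 0.52 SD, so the bias runs against ACT.
- As in the first case, but with 17% ACT dropout who would have improved 0.3 SD. Everyone followed: (0.83 × 0.6 + 0.17 × 0.3) − 0.168 = 0.38 SD. LOCF: 0.498 − 0.083 = 0.41 SD (0.415 before rounding).

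**The case against.** **These controls are not lost to the analysis.** A reader might infer that they drop out of the data and that intention-to-treat is broken. The documents do not support that. Everyone randomised is kept and analysed as assigned, and telling participants that they may withdraw breaches nothing. What can be lost is the observed week-12 score, which leaves intention-to-treat intact in form but weaker in substance.

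**The sentence grants a permission.** It does not require a treated control to leave, and it does not say that such a control will not be approached. The follow-up sentence covers all participants, and the Discussion plans general retention efforts. This stands, and it is why the problem is a poor fit between two sections rather than a flat contradiction.

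**The direction is not established.** A reader might infer that ACT is flattered. One such scenario takes 17% leaving, 0.4 SD improvement in controls who stay and 0.8 SD in those treated: 0.83 × 0.4 + 0.17 × 0.8 = 0.468 against 0.332, a gap of 0.136 SD. But 0.8 SD has no source in the documents, and half the gap (0.17 × 0.4 = 0.068) is natural course that LOCF removes from any missing control. The scenario also allows no ACT dropout, although the plan applies its allowance to every group. With 17% of ACT participants who would also have improved 0.8 SD carried forward, the net bias is 0. This objection stands in full. It does not remove the concern, because two unknown biases that happen to cancel are no safeguard.

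**What controls are actually told is in material not shown.** True. If the information sheet already separates care-seeking from withdrawal, only the article's sentence needs aligning.

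**Conclusion.** The point holds in a limited form. The Discussion couples care-seeking by controls with study exit, and this sits badly with the aim in Data analysis of obtaining and analysing everyone's outcomes. With two control assessments and LOCF, a control who leaves and is not reached is scored as unchanged, and this enters both ACT-versus-control contrasts.

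The size is an assumed range, not an estimate: about +0.03 to +0.15 SD towards ACT for 14% to 30% leaving who would have improved by 0.25 to 0.5 SD; zero if they would not have changed; and about −0.03 to −0.08 SD if they would have worsened by 0.25 SD. These ranges assume no ACT dropout. LOCF on ACT dropouts can cancel or reverse a shift towards ACT. Neither a one-directional bias nor a breach of intention-to-treat can be claimed. The change is still worth making, because it is cheap and concerns what is collected.

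**What to change.** Reconcile Data analysis with the limitations part of the Discussion, and carry the same wording into what controls are told:

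1. Seeking treatment does not require leaving the study assessments.
2. Controls who seek treatment will still be invited to the 12-week questionnaires.
3. Withdrawal from data collection remains possible at any time and is a separate choice.
4. The existing psychological-support item is repeated at the second assessment in all arms, worded to cover the period since baseline.
5. Observed scores are analysed in the randomised group, whatever care was received; LOCF then applies only to those who decline or cannot be reached.

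Access to care is unchanged. The cost is a revision of the information wording and one repeated item. The contrast will be slightly diluted by outside care among controls, which is what the stated intention-to-treat principle implies.
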